# SCIENTIFIC JUSTIFICATION

## Current knowledge

### Pathology/ health problems and current knowledge

Physical activity and sport play an important role in the military, as they are used to develop and optimize the operational capacity of combatants. In France, *Entraînement Physique Militaire et Sportif* (Physical and Sport Training for the Military) is designed to enable all military personnel to acquire the physical and mental capacities they need to perform their duties (Etat-major des armées - Centre national des sports de la défense, 2011). In addition, the preservation of operational capacity throughout a military career is based, among other things, on the health benefits of sporting activities, notably with respect to the prevention of chronic, stress-related pathologies such as cardiovascular disease and depression (World Health Organization, 2003).

Nevertheless, physical activity and sport can also be the source of acute (sprains, fractures, etc.) and chronic (tendinopathies) musculoskeletal pathologies. In particular, there is a high rate of lower-limb trauma during physical activities in the military context, both among young enlisted personnel [15–20%] (At, 2016; Bauvent, 2014; Pleche, 2018) in operational military units or during selection courses for specialized units [30–45%] (Bertrand, 2016; Brocard, 2014; Chipault, 2016; Longin, 2015; Morinière, 2013). In addition to their impact on the health of combatants, these injuries have a negative impact on the operational capability of forces (due to incapacity) and a significant economic cost (Ressort, Desjeux, Marsan, & Thevenin-Garron, 2013)

Identifying risk factors is an essential step in developing an injury prevention strategy. Classically, there are two categories of risk factors: (*i*) those that are intrinsic to the individual, and include age, gender, physical condition or tobacco consumption; and (*ii*) extrinsic factors, which relate to the context in which the sporting activity is performed, and which include environmental conditions (temperature, humidity, etc.), the type of activity, or training conditions (progression, regularity, etc.). (Bigard, Cravic, & Banzet, 2010; Meeuwisse, 1994; Williams, 1971). The identification of modifiable risk factors (i.e. those that are amenable to an intervention that will reduce the likelihood of injury), remains a major challenge in the field of sport (Bahr & Holme, 2003).

Against this background, the POSITION project aims to study the cognitive mechanisms involved in body awareness, both as a risk factor in fall injury, and as a target for a prevention strategy that aims to reduce the injury rate by improving postural control.

This research project was prompted by epidemiological observations carried out during the French Marine Commando Selection Course (STAC). Medical unfitness due to incapacity is the leading cause of failure (70%). Acute trauma is the principal pathology (60%), typically involving the lower limbs (Bertrand, 2016; Longin, 2015; Morinière, 2013). A review of the circumstances surrounding the trauma highlighted that a fall due to a loss of balance was the cause in 90% of cases (Bertrand, 2016). These data suggest that postural balance could play a role in the injuries encountered during the STAC. The activities that candidates must undertake require them to have extremely good postural balance: trainees carry heavy loads (a combat bag and a weapon, weighing 15 kg) for prolonged periods, and complete extreme challenges that are run at-height in all weather conditions. Epidemiological data collected during the course show that the leading activity resulting in trauma is the ‘jungle’ challenge, which involves overcoming obstacles up to 5 meters high with no safety net (Morinière, 2013). Moreover, preliminary (unpublished) epidemiological data collected from other military units (the National Gendarmerie, the 1st Marine Infantry Parachute Regiment, the 13th Parachute Dragoon Regiment, the 10th Air Parachute Commando, and the Fusiliers Marins [Navy Riflemen] School, Paris Fire Brigade) seem to confirm the high rate of trauma linked to a loss of postural balance during physical activities.

It should be noted that the physical activities carried out by the aforementioned military units are characterized by a very high level of physical and psychological demands, which challenge the individual’s physical capacities and exposes them to a high level of stress. The individual’s limits are pushed to the extreme by demanding and intense physical exercises (each exercise being carried out in combat gear). Another challenge is the constant psychological testing (ongoing stressors such as a lack of sleep, uncertainty about what the day will hold, etc.), which ensure that only the best candidates are selected for the missions undertaken by elite military units (Bertrand, 2016). Together, these challenges activate the neurobiological stress response. The latter, aspecific biological mechanism is a response to both psychological or physical stress; it enables the organism to cope with changes in its environment that affect its integrity, and to adapt if these changes persist. It depends not only on the characteristics of the stressor, but also on the subject’s general psychobiological response.

### Current knowledge of the issues addressed by the protocol

Several neurophysiological systems contribute to postural balance, which is more than the reflexive action of the postural muscles. Postural balance involves various high-level cognitive processes such as attention, visuo-spatial perception and executive functions (Amboni, Barone, & Hausdorff, 2013). Sensory information from peripheral receptors (located in the visual, vestibular and somatosensory systems) is integrated by the central nervous system, which, in turn, controls the muscles that orient the various parts of the body with respect to gravity (Forbes, Chen, & Blouin, 2018). The cognitive mechanisms involved in postural awareness refer to the attention that the individual pays to information from somatosensory and vestibular systems (Mehling et al., 2009). The more attention that the individual pays to his or her body, the more information is available to them to control their posture. In other words, it is possible that postural control may be enhanced by a high level of body awareness. In the context of the POSITION project, we hypothesize that the individual level of postural awareness could modulate the risk of fall-related trauma. In particular, we propose that a low level of awareness could be a risk factor for fall-related trauma, *via* impaired postural control. Furthermore, we hypothesize that improving postural control, by increasing the level of postural awareness, could be a primary prevention strategy.

It should be noted that the neurophysiological systems involved in postural control are influenced by brain structures that are not part of the postural control loop. For example, the degree of excitability of the postural myotatic reflex at the level of the spinal cord is modulated by subcortical structures (notably the periaqueductal gray matter and the amygdala) that are activated during the stress response (Volchan et al., 2017). Interestingly, body awareness plays an important role in regulating the stress response by contributing to the identification, evaluation and regulation of the body’s internal physiological state that characterizes the neurobiological stress response (Craig, 2002). These observations suggest that postural balance may be indirectly modulated by cognitive mechanisms governing body awareness, *via* control of non-postural responses (e.g., the stress response) that influence posture. In sum, the body awareness mechanism could modulate the occurrence of fall injuries either: (*i*) directly as a central actor in the postural control loop; or (*ii*) indirectly by acting on non-postural pathways that affect posture. Figure 1 summarizes the theoretical model we will be testing in the context of the POSITION project.

[figure not shown]

**Figure 1** – The theoretical model according to which cognitive mechanisms governing body awareness could modulate the occurrence of fall injuries, either: *(i)* directly by acting on descending motor pathways (black arrow) as body awareness is a central process in the postural control loop (solid black lines); or *(ii)* indirectly by controlling non-postural pathways (grey arrow) such as the stress response which alters postural control.

Classically, quiet standing is described by the biomechanical ‘inverted

Classically, ‘quiet standing’ is described by the biomechanical ‘inverted pendulum’ model (Gage, Winter, Frank, & Adkin, 2004): the body moves continuously along an antero-posterior axis and a medio-lateral axis, both of which originate in the medial malleoli of the ankles (Figure 2). The standing position is naturally unstable due to the physiognomy of the human body (⅔ of body mass is located in the upper ⅔ of body height), and endogenous physiological disturbances (breathing, heartbeats, etc.). Postural control is therefore continuously deployed to maintain the body around a point of equilibrium, and consequently avoid a fall.

[figure not shown]

medio-lateral

oscillations

antero-posterior

oscillations

**Figure 2 –** Biomechanical model of static postural balance, also known as the ‘inverted pendulum’ model. The body moves continuously along an antero-posterior axis and a medio-lateral axis, both originating in the medial malleoli of the ankles.

In the context of sports medicine, static postural balance is most often assessed by the Balance Error Scoring System (BESS) (Delahunt et al., 2018; Docherty, Valovich McLeod, & Shultz, 2006). This clinical test must be performed by a physician, and lasts around five minutes. In the field of cognitive neuroscience, recent work has shown the value of a paraclinical tool, posturography, to assess postural balance and investigate the individual’s level of body awareness (C. Verdonk, Trousselard, Medani, Vialatte, & Dreyfus, 2020). The analytical tools developed in the context of the latter study were subsequently used to develop another tool to assess the risk of fall injury during the STAC. Preliminary analyses show that posturography was able to correctly assess the risk of injury in 75% of trainee marine commandos (C. Verdonk et al., 2019).

The POSITION project focuses on the role of cognitive mechanisms governing body awareness as a risk factor for fall injuries during physical activities in the military. In this context, there is a clear need to evaluate the modifiability of the latter risk factor in order to develop a prevention strategy. ‘Modifiability’ means that the risk factor is amenable to an intervention that will modulate its influence on the occurrence of injury (Bahr & Holme, 2003). Specifically, the project will test the effect of *Potential Optimization Techniques* (POTs) on the cognitive mechanisms governing body awareness. We hypothesize that POTs will increase body awareness, and thus reduce the risk of fall-related injury, *via* improved postural control.

POTs were created in the 1990s by Doctor Edith Perreault-Pierre to meet needs that had never before been addressed in the armed forces: mental preparation and recovery. (Etat-major des armées - Centre national des sports de la défense, 2011). Initially developed to meet the requirements of the French Air Force regarding stress management and human factors (in the context of flight safety), they are now being deployed throughout the French Army’s other corps.

POTs are defined as a preparation method that is focused on learning a set of mental techniques and strategies that will help the individual to use their physical and psychological resources as effectively as possible, as a function of the demands of the situation they find themselves in (Figure 3).

**Techniques**:

A set of resources or tools that support the best performance possible

**Potential**:

The strengths, capacities, abilities and resources available to the subject.

**Optimize**:

Help in motivating the individual to perform as well as possible as a function of the demands of the situation

**POT**

Context

Context

Context

**Figure 3 –** The 3 components making up Potential Optimization Techniques (POTs).

The techniques draw upon basic procedures found in high-level sport. The method takes the form of a customizable ‘toolbox’ and the aim is to enable trained personnel to complete their missions successfully, while preventing the deleterious effects of stress. On the one hand, the positive effects of mental imagery, internal dialogue, relaxation and mindfulness techniques on performance, health and well-being are well documented in the literature (Pagninia, Manzonib, Castelnuovoab, & Molinariab, 2013; Vealey & Greenleaf, 2010; William, Zinsser, & Bunker, 2010). On the other hand, evidence regarding the effectiveness of POTs is inconclusive. The Table included in APPENDIX 1 summarizes studies that have evaluated the effects of POT training on psycho-cognitive and physical performance, stress and sleep. Although the quality of these studies varies (several before-and-after interventional studies, and one randomized controlled trial), taken together, the results support the clinical and operational benefits of POTs.

## Research hypotheses

The POSITION project aims to evaluate the effectiveness of POTs in preventing fall injuries following a loss of balance^[[2]](#footnote-2)^. We hypothesize that POTs could reduce the risk of fall injury by improving postural control through improved postural awareness.

## Expected benefits

In the military context, physical activities are associated with a high rate of fall-related injuries. Consequently, a key challenge for military medics is to identify individuals who are at-risk, in order to be able to offer them personalized preventive countermeasures to reduce their risk. There is a need to develop a tool that can assess risk factors that are amenable to a prevention strategy that reduces the risk of injury. One of the outcomes of the POSITION project will be the development of a tool to identify individuals at-risk of fall injury, based on a postural balance analysis (assessed using the BESS and posturography).

In addition, the investigation of the cognitive mechanisms involved in postural awareness will provide a better understanding of inter-individual variability regarding fall injury risk during physical activities in the military context. Finally, an assessment of the ability of POTs to reduce the risk of injury will support the evaluation of the program, which is already used by the French armed forces, in preventing fall-related trauma.

# OBJECTIVES

## Main objective

The main objective is to evaluate the effectiveness of POTs in preventing fall injuries during physical activities in the military context. To this end, we will analyze the effect of a POT intervention on the rate of fall-related injuries that occur during physical activities in a military population, compared to an active control.

## Secondary objectives

The study has 4 secondary objectives:

1. The first is to test the mechanistic hypothesis that POTs reduce the risk of fall-related injury by improving postural awareness.
2. The second is to test the mechanistic hypothesis that POTs reduce the risk of fall injury by decreasing the intensity of the psychobiological stress response during physical activities in the military context.
3. The third is to use machine learning techniques to develop a predictive model of the risk of fall injury, based on a clinical test (BESS) and paraclinical (posturography) measurements taken before physical activities begin.
4. The fourth is to evaluate the persistence over time of the effectiveness of a POT intervention in reducing the risk of fall injury. The assessment will be based on participants who continue to engage in physical activities after the end-of-study visit (and who complete the selection course); the analysis will compare the rate of fall injuries for POTs and active control groups.

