### Summary

[figure not shown]

**Figure 4** – Schedule of the study for a given year. The same schedule will be followed during the two years of the study, only the content of the sessions will change: the active control in year Y, and the POTs intervention in year Y+1. Timeline for each study participant (in weeks). V1: inclusion visit (saliva sampling, posturography, and the BESS). V2: end-of-study visit (saliva sampling, and posturography). Gray triangle: a one-hour session, either during the active control program (first year), or the ORAF intervention (second year). Star: Self-administeed questionnaires (PAS, PSS, fatigue).

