### Follow-up visits

A follow-up visit will be carried out just before each session of the POTs and active control interventions (the schedule for which is shown in Figure 4). During the follow-up visit, the participant will complete self-report questionnaires measuring postural awareness (the Postural Awareness Scale) and perceived stress (Cohen’s Perceived Stress).

Participants who suffer a fall trauma during the course will attend an additional follow-up visit, which will take place on the day of the injury. The military medic, or one of his or her assistants, will collect medical information relating to the trauma, and carry out a posturography measurement. The participant will then complete questionnaires measuring postural awareness (the Postural Awareness Scale) and perceived stress (Cohen’s Perceived Stress).

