## Data collected

### Clinical parameters

Clinical data collection will be limited to injury history, age, sex, height and weight. These data will be recorded using posturography software.

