**Analysis of the main objective**

The effect of the intervention (POTs *vs.* active control) on the rate of fall injuries will be evaluated using a comparative survival analysis (the Cox model, with clinical variables as potential confounders). Survival curves for POTs and active control groups will be compared using the log-rank test.

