**Analysis of secondary objectives**

For the first secondary objective, the effect of the POTs intervention on postural awareness will be evaluated by comparing the following for the POTs group: (*i*) scores on the Postural Awareness Scale at the six measurement times (repeated measures ANOVA), and (*ii*) posturography measurements pre- and post-intervention (paired samples comparison of means).

For the second secondary objective, the effect of the POTs intervention on the psychobiological stress response will be evaluated by comparing the following measures for the POTs group at all six measurement times: (*i*) scores on Cohen’s Perceived Stress Questionnaire (repeated measures ANOVA), and (*ii*) biological stress variables (paired samples comparison of means).

For the third secondary objective, machine learning will be used to evaluate the accuracy of the predictive model of the risk of fall injury using the following calculation:

|  | $\text{Accuracy=}\frac{\text{True }\text{Fall-related injury }\text{participants + True }\text{Non-fall }\text{participants}}{\text{Total number of participants}}$ |  |
| --- | --- | --- |

where N_prediction of trauma_ is the number of participants for whom the machine learning model predicts the occurrence of a fall injury and who do, in fact, suffer a fall injury during the selection course; N_prediction of_ _good health_ is the number of participants for whom the model predicts the non-occurrence of a fall injury and who do not, in fact, suffer a fall injury during the selection course; and N_total_ is the total number of participants included in the study.

For the fourth secondary objective, the long-term effectiveness of the POTs intervention in preventing fall injuries between the end of the study and the end of the selection course will be evaluated using a comparative survival analysis (the Cox model). Survival curves for POTs and active control groups will be compared using the log-rank test.

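### Objectives 1 and 2 are worded as mechanisms by which POTs prevent injury, but the analyses fixed for them test only change over time within the POTs group and never involve injury

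*Protocol*

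**What the plan says.** Protocol, Secondary objectives, words the first objective as "The first is to test the mechanistic hypothesis that POTs reduce the risk of fall-related injury by improving postural awareness" and the second as "The second is to test the mechanistic hypothesis that POTs reduce the risk of fall injury by decreasing the intensity of the psychobiological stress response". The Research summary repeats both.

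Protocol, Analysis of secondary objectives, fixes the methods. For objective 1, "the effect of the POTs intervention on postural awareness will be evaluated by comparing the following for the POTs group": Postural Awareness Scale (PAS) scores by repeated-measures ANOVA, and posturography by a paired comparison of means. For objective 2, "the effect of the POTs intervention on the psychobiological stress response will be evaluated by comparing the following measures for the POTs group": Perceived Stress Scale (PSS) scores by repeated-measures ANOVA, and the saliva markers by a paired comparison.

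The injury analysis is separate. Analysis of the main objective specifies "the Cox model, with clinical variables as potential confounders", and Clinical parameters defines what is available for that: "Clinical data collection will be limited to injury history, age, sex, height and weight".

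On timing, Follow-up visits says "A follow-up visit will be carried out just before each session of the POTs and active control interventions", and PAS and PSS are completed then. Repeat posturography is taken on the day of a fall injury and at the end of study. Repeat saliva is taken at the end of study only. The legend of Figure 4 lists "V2: end-of-study visit (saliva sampling, and posturography".

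**The concern.** Each objective claims three things: POTs change a mediator (awareness or stress), the mediator bears on injury, and POTs thereby lower injury. The planned tests look only at whether the mediator moves over time among people who all received POTs. The step from mediator to injury is not examined, and the first step has no comparator.

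The protocol leans on the missing step. Its background section treats body awareness as a modifiable risk factor for fall injury, and the Benefits section says the study will describe how awareness and the stress response bear on injury. A rise in PAS or a fall in PSS could then be written up as evidence of mechanism when the analysis shows only that scores changed during a demanding selection course.

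**Working it through.** **1. Which planned analysis contains what.**
- Main objective: Cox model and log-rank test, group against injury, adjusted for injury history, age, sex, height and weight. No awareness or stress measure.
- Objective 1: PAS and posturography against time, POTs group only. No injury, no control group.
- Objective 2: PSS and saliva markers against time, POTs group only. No injury, no control group.
- Objective 3: injury predicted from BESS and posturography taken before the course. No awareness, no stress, no change in balance.
- Objective 4: group against later injury. No awareness or stress measure.

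No line holds both a mediator and injury.

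**2. What the planned result can distinguish.** Take two cases with the same PAS rise in the POTs group. In one, injury is 50% in both groups. In the other, it is 50% under control and 35% under POTs, with the reduction acting through PAS. The objective 1 analysis gives the same answer in both. The main Cox model separates the two cases on injury, but does not show that PAS carried the difference.

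**3. Order in time.**
- PAS and PSS: before sessions, in both groups, so they can precede an injury.
- Posturography: baseline, then on the day of injury (after the fall), then at the end-of-study visit.
- Saliva: baseline, then the end-of-study visit.

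For anyone injured in the three-week window, every scheduled repeat balance or saliva measure follows that person's first injury. At the plan's rates and with 180 evaluable per group, that is 180 × 0.35 = 63 POTs participants and 180 × 0.50 = 90 controls. For them the post-intervention value may reflect the injury itself.

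**4. How many injuries are available.** Objectives 1 and 2 have no sample size of their own, so the figure to reproduce is the primary one: 50% against 35%, two-sided 0.05, power 0.80.
- n = [1.960 × √(2 × 0.425 × 0.575) + 0.842 × √(0.50 × 0.50 + 0.35 × 0.65)]² / 0.15² gives 170 per group, or 183 with continuity correction.
- Allowing for 10% drop-out: 183 / 0.90 = 204, or 183 × 1.10 = 202. The stated 200 agrees closely.
- Evaluable: 200 × 0.90 = 180 per group.
- Expected injuries: 90 + 63 = 153.

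**The case against.** The strongest reply is that the plan does not have to be read as claiming mediation from these tests alone. The analysis section describes them only as effects on awareness and on the stress response. A change in the mediator is a necessary link, so no change would count against the mechanism, and a null primary result would too. That stands: the tests can weaken the hypothesis. They cannot confirm it, and the objectives as worded say that it will be tested. This is not a detail left for a later document, because the protocol states both the hypothesis and the method and the two do not match.

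A reader might infer more than the protocol supports, in three ways:
- That neither objective can be answered from this trial. PAS and PSS are collected before sessions in both groups, so the gap lies in the analyses, not in the data.
- That balance is re-measured only after the injury window. Injured participants have posturography on the day of injury, inside the window, and the end-of-study measurement precedes the injuries counted for objective 4. The timing limit is narrower: no repeat measure comes before a participant's own first injury in the primary window. For objective 2 it applies to saliva, since balance is not one of its criteria.
- That 170 injuries are available (200 × 0.50 + 200 × 0.35). The 200 already includes the drop-out allowance, so about 153 is the fair figure.

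It is also fair to say that a mediation model would be fragile here. Hazard ratios are non-collapsible, so with 35% to 50% of participants injured the POTs hazard ratio can shift when a prognostic score is added, even without mediation. Under Randomization, all controls come from one year and all POTs participants from the next, so an apparently mediated effect could be a difference between years.

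**Conclusion.** The mismatch is real. As planned, objectives 1 and 2 can show only that awareness, perceived stress, balance and saliva markers changed over time in the POTs group. They cannot show that POTs caused the change, nor that it bears on injury. Posturography and saliva cannot explain primary-window injuries because of when they are taken.

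The primary analysis is untouched, so this affects secondary claims and should be corrected before those claims are made. The 153 injuries assume the plan's 50% and 35% rates and that the 10% who drop out contribute no events. Fewer will be informative, because the first two sessions are placed at the very start of the course and the latest score before an early injury will be close to baseline.

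**What to change.** 1. Compare change in PAS, PSS, posturography and the saliva markers between the POTs and active control groups, in place of the POTs-only tests. Mark which repeat posturography and saliva values were taken after an injury.
2. As a supportive analysis, fit a Cox model in both groups with the latest pre-injury PAS score as a time-updated covariate, adjusted for group, the baseline score and the clinical variables. Fit a second, separate model for PSS. Report the score's hazard ratio with its interval. Do not present a shift in the POTs hazard ratio with and without the score as proof of mediation.
3. Unless the score is shown to relate to later injury, report objectives 1 and 2 as effects on awareness and stress, not as mechanism.

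Before step 2, settle how many pre-session scores there will be. The Research summary gives four follow-up visits, while the Follow-up visits section implies one before each of the six sessions.

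The cost is a few extra models on data already collected, and a more modest claim. Even then, the mediator–injury association is open to unmeasured confounding, and the between-group comparison to differences between the two years.
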